### Randomization and Blinding

The head of each hospital and the relevant department will recruit participants. Eligible children with myopia will be randomly assigned on a 1:1 basis to either a *tuina* therapy intervention group or a drug positive control group. Randomization will be conducted by the head of each hospital using a computer-generated random number generator. Upon the entry of qualified trial participants, the hospital head will assign them to the respective groups according to the randomly generated numbers and follow the corresponding medical instructions without any modification. There are 2 types of interventions in this study. It is difficult to implement blinding for both the therapists and the parents or legal guardians of the children. Nevertheless, the outcome assessors will use blinding for the randomization, intervention procedures, and result analyses.

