**Methods:**

This study is a multicenter randomized controlled clinical trial. A total of 62 children with myopia will be recruited from 4 hospitals and randomly assigned in a 1:1 ratio to a *tuina* experimental group and a drug-positive control group (tropicamide eye drops). Treatments in each group will be administered 3 times per week for a total of 8 weeks. The *tuina* experimental group will receive 20 minutes of *tuina* therapy per session, while the drug-positive control group will receive tropicamide eye drops administered every other day, with 2 drops per session. The primary outcome measures include uncorrected visual acuity and axial length, while secondary outcome measures include refractive power and accommodative amplitude. Data will be collected at baseline (week 0), on the day of completion of weeks 4 and 8 of treatment, and at the end of the 10-week follow-up period. Adverse events will be monitored and recorded throughout the study. Statisticians will be blinded. Data will be analyzed using SPSS version 28.0.

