### Participants

#### Recruitment Strategy

This study will recruit 62 participants through recruitment notices in communities and hospitals from the Second Affiliated Hospital of Yunnan University of Traditional Chinese Medicine, Baoshan Hospital of Chinese Medicine, Shiping Hospital of Chinese Medicine, and Zhaotong Hospital of Chinese Medicine. Recruitment will be conducted by physicians from the *tuina* departments of hospitals. Appropriate compensation will be provided to participants upon completion of the entire procedure. Moreover, the parents or legal guardians of the participants have the right to withdraw from this study at any time and for any reason without facing discrimination or difficulties in the hospital. Participants must be children with myopia and must meet the following inclusion criteria.

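### The hospital head recruits, runs the random number generator and assigns the groups, so allocation concealment is not secured at the recruiting sites

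*Protocol article*

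**What the plan says.** The Randomization and Blinding section of the protocol article gives the hospital head three tasks:

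- Recruiting, shared with the department: "The head of each hospital and the relevant department will recruit participants".
- Producing the sequence: "Randomization will be conducted by the head of each hospital using a computer-generated random number generator".
- Assigning, once a qualified child enters: "the hospital head will assign them to the respective groups according to the randomly generated numbers".

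The only safeguard named is that the head will "follow the corresponding medical instructions without any modification".

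The Recruitment Strategy section describes recruiting differently: "Recruitment will be conducted by physicians from the" *tuina* departments of the hospitals.

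On blinding, Randomization and Blinding says: "It is difficult to implement blinding for both the therapists and the parents or legal guardians of the children". It adds that "the outcome assessors will use blinding for the randomization, intervention procedures, and result analyses". The abstract says "Statisticians will be blinded", and Data Management and Quality Control has data entered twice by two members who do not know the grouping.

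**The concern.** Concealment means that whoever decides whether and when a child enters the trial can neither know nor influence the next assignment. Here the role that recruits also holds the generator and makes the assignment. If recruiting is really done by the *tuina* physicians, they belong to the department that delivers the experimental treatment, and nothing states that the site-held sequence is kept from them.

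At stake is the comparability of the arms at baseline. If milder or more cooperative children entered one arm more often, the comparison would be biased before any outcome was measured. Adjustment for recorded baseline values could remove part of such an imbalance, but not the part due to unrecorded factors such as cooperation.

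Those enrolling may well prefer one arm. The Objectives section expects *tuina* to be safer than the drug, and the Results section reports, while enrolment continues, that the data so far favour *tuina*. Study Design calls this a noninferiority trial, so a prognostic shift towards the *tuina* arm would help the conclusion that the study hopes to reach.

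**Working it through.** The point is procedural, so the main check is to set the statements against what concealment requires. The arithmetic afterwards only gives a sense of scale.

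**Step 1: who does what, on each reading of who recruits**

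- *Randomization and Blinding as written.* The head recruits (with the department), generates and assigns. Enrolment and sequence are not separated.
- *Recruitment Strategy as written.* *Tuina* physicians recruit, and the head of the same hospital generates and assigns. Recruiter and sequence holder may be different people, but both are at the same site and no barrier between them is stated.

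Neither reading secures concealment.

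**Step 2: how the weakness could act**

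The article does not say whether the numbers are listed beforehand or drawn at each entry.

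- If listed beforehand, the holder could see the next assignment.
- If drawn at entry, the holder could repeat the draw.

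Only one of these can apply to a given child. Against either, the plan offers no more than the undertaking to follow the numbers unchanged.

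**Step 3: the plan's own sample size**

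Inputs from Sample Size: effect size 0.8, two-sided α = 0.05, power 80%, ratio 1:1. The two-sample t test needs 25.52 per arm, so 26 per arm and 52 in all, with a power of 80.7%. The stated 52 is reproduced. It supplies the 26 per arm used in step 5.

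**Step 4: does the split so far show a problem?**

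Inputs from Results: 29 enrolled, 16 *tuina* and 13 control. Under fair 1:1 allocation, the two-sided exact probability of a split at least this uneven is

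2 × P(X ≥ 16), with X ~ Binomial(29, 0.5), = 0.71.

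The split fits fair allocation. It neither supports nor rules out selective entry, because children can be steered between arms without changing the arm sizes much.

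**Step 5: illustration of size, under assumption**

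The documents give no figure for a prognostic shift, so a range is assumed: d = 0.1, 0.2 or 0.3 SD between the arms, with no true treatment difference. The test is the two-sided 5% comparison used in Sample Size and Data Analysis, by normal approximation.

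- SE of the standardised difference = √(2/26) = 0.277.
- False-positive rate = 1 − Φ(1.96 − d/SE) + Φ(−1.96 − d/SE).
- d = 0.1: d/SE = 0.36, rate 6.5%.
- d = 0.2: d/SE = 0.72, rate 11.1%.
- d = 0.3: d/SE = 1.08, rate 19.1%.

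**Step 6: how many children can still be protected**

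62 − 29 = 33 children, which is 33/62 = 53% of the planned total, as of December 2025.

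**The case against.** *The article is condensed, and a fuller protocol may describe concealment.* That would excuse missing detail such as envelopes or block sizes. It does not excuse a positive statement that the recruiting role generates and assigns. A fuller document with independent allocation would contradict the article, and the article would still need correcting. For the same reason, the article's silence on blocking or stratification is not held against it. Chance imbalance under simple randomisation is a different matter from concealment and does not bias the comparison.

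*Assignment follows qualification, and the head promises not to modify it.* The order of events is right and counts in the plan's favour. But eligibility is judged at the site that holds the sequence, and a promise is not a barrier.

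*Recruiters and sequence holder may be different people.* This stands in part. The conflict between the two sections leaves it uncertain whether one person does everything, but it does not supply the missing separation.

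*Much of the trial is blinded.* This stands. A reader might infer a fully open-label trial, and the documents do not support that: assessors, statisticians and data-entry staff are to be blinded. Those measures limit bias in measuring, entering and analysing outcomes. They do not act on who enters which arm. The wording that assessors are blind to the randomization concerns assessors, not those who enrol.

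*Foreknowledge or redrawing is inferred.* This also stands. A reader might infer that the head does know the next assignment or does redraw. The article says neither; it only fails to prevent them.

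**Conclusion.** The concern holds as a weakness in a stated procedure. The article places the sequence and the assignment at the recruiting site, in the hands of a role that one section also makes a recruiter, with no safeguard beyond a promise. Allocation concealment is therefore not secured, and selection bias at enrolment is possible because therapists and guardians are unblinded. The two sections also disagree on who recruits.

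A reader might go further and conclude that allocation has been manipulated or that the data collected so far are biased. The documents do not support that: 16 v 13 is what fair 1:1 allocation readily produces (p = 0.71), and nothing is said about how any individual child was assigned.

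The size of any bias cannot be derived from the documents. The figures of about 6.5%, 11% and 19% rest on assumed shifts of 0.1 to 0.3 SD, 26 analysed per arm and a normal approximation; they illustrate and do not estimate. It would be unsafe to express the shift as a share of the planning effect, because the 0.8 in Sample Size is taken from an expected efficacy rate above 80%, and its standing as a difference in SD units is doubtful.

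The point should be settled before further children are allocated, because concealment cannot be restored after enrolment.

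**What to change.** For all children still to be allocated (33 as of December 2025):

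1. Have an existing person outside the *tuina* departments generate and hold the sequence. That person should not recruit, treat, assess or enter data and, since statisticians are to be blinded, should not be the trial's analyst.
2. Release each assignment by telephone or online, only after consent, eligibility and baseline measurements have been recorded.
3. Do not place the list with the office that receives the case report forms. According to Data Management and Quality Control, that office is the Department of Tuina Basic Education. It is not evidently independent of the experimental therapy, and holding the list there would put the blinding of data entry at risk.
4. Reconcile Recruitment Strategy with Randomization and Blinding on who recruits.
5. Report how the first 29 children were assigned: whether numbers were listed beforehand or drawn at entry, who could see them, and when eligibility was recorded relative to assignment. A comparison of children allocated before and after the change may be shown, but with 29 and 33 children it has little power and cannot stand in for this account.

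Cost: a short amendment, one call or log-in per child, and a change of method during the trial that must be reported. No extra visits or measurements are needed.

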### Intervention

#### Selection of Therapists and Participants

To ensure that all *tuina* manipulation in this study conforms to standardized procedures, the therapists involved possess physician qualifications and a master’s degree in pediatric *tuina* and have undergone unified training in the *tuina* techniques used in this study. Only those who successfully complete the training are eligible to participate. During the course of the experiment, children with myopia are generally not allowed to use any other interventions. If participants adopt other interventions during this period, they will be defined as noncompliant and withdrawn from the experiment.

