**Conclusions:**

This study aims to evaluate the efficacy and safety of *tuina* therapy in the treatment of adolescents with myopia. We hypothesize that the therapeutic effect of *tuina* therapy is noninferior to that of tropicamide eye drops, with the additional advantages of fewer side effects and stable long-term efficacy, thereby providing reliable evidence and support for the application of *tuina* therapy in the management of myopia in adolescents.

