## Methods

### Study Design

This study is designed as a multicenter randomized controlled noninferiority trial to be conducted from June 2025 to October 2026. We plan to recruit 62 participants from 4 hospitals in Yunnan Province. Eligible participants will be randomly assigned in a 1:1 ratio to the *tuina* experimental group and the positive drug control group (tropicamide eye drops). Each participant will undergo an 8-week treatment period followed by a 2-week follow-up. Baseline information and outcomes will be assessed at baseline, at the completion of weeks 4 and 8 of treatment, and at the end of the 10-week follow-up (Figure 1). This trial adheres to the guidelines of the SPIRIT (Standard Protocol Items: Recommendations for Interventional Trials).

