### Sample Size

Using G*Power software to calculate the sample size, based on the preliminary pilot study results, the expected efficacy rate in the manipulation treatment group is above 80% (*P*<.05). Therefore, we set an expected effect size of 0.8. To detect between-group differences with 80% statistical power (*β*=.20), we choose a 2-tailed α level of .05. With an allocation ratio of 1:1, the required sample size was 52 participants (26 per group). Considering a 20% expected dropout rate, the final sample size was set at 62 participants (31 per group).

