### Data Analysis

All data will be analyzed using SPSS version 28.0 and GraphPad Prism version 10.3.1 statistical software. For normally distributed data, results will be described as mean (SD) and analyzed using the *t* test. For nonnormally distributed data, results will be described as median (IQR) and analyzed using the Wilcoxon rank sum test for within-group comparisons and the Mann-Whitney *U* test for between-group comparisons. A 2-sided *P* value of .05 will be considered statistically significant. Missing data will be handled using expectation maximization, last observation carried forward, or listwise deletion.

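### Children who take up another intervention are withdrawn after randomisation and the missing-data method is left open among three, so the noninferiority comparison can be biased in either direction

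*Protocol article*

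**What the plan says.** The section on selection of therapists and participants sets the rule on other treatments: "During the course of the experiment, children with myopia are generally not allowed to use any other interventions". It continues: "If participants adopt other interventions during this period, they will be defined as noncompliant and withdrawn from the experiment". The article does not say whether these children still attend the week 4, 8 and 10 assessments, or whether they stay in the analysis.

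The Data Analysis section states: "Missing data will be handled using expectation maximization, last observation carried forward, or listwise deletion". It gives no order of preference and no condition for using one method rather than another.

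Three other places bear on this. Study Design fixes the aim: "This study is designed as a multicenter randomized controlled noninferiority trial to be conducted from June 2025 to October 2026". Randomization and Blinding accepts that therapists and guardians can hardly be blinded. Sample Size expects 20% dropout among 62 children.

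**The concern.** Taking up another intervention happens after randomisation. It plausibly follows disappointment with the child's vision, and in an unblinded family it can also follow from knowing the assigned treatment. The children lost may therefore differ between arms in number and in kind, and randomisation no longer protects the comparison of those who remain. The wording of the prohibition (generally not allowed) also leaves room for judgement about who is withdrawn.

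The three methods rest on different assumptions. LOCF assumes that nothing changes after the last visit. Listwise deletion compares completers only. EM relies on data missing at random, and if it is used to fill in one dataset that is then given to a t test, the filled values count as observed and the standard error is too small. With no selection rule, the choice can be made once the data are known. That risk is practical: the Results section already reports favourable impressions of visual acuity and axial length with 29 children enrolled.

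At stake is the false-noninferiority rate, nominally 2.5%. An analysis plan can later narrow the choice of method, but it cannot recover outcomes that were never measured.

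**Working it through.** **The plan's own figure.** Sample Size gives "Therefore, we set an expected effect size of 0.8", 80% power and "we choose a 2-tailed α level of .05". A two-sample t test with d = 0.8 needs 25.5, so 26 per arm and 52 in total (power 0.807), as stated. The final 62 is 52 × 1.2 = 62.4, rounded down. Planned dropout is 0.20 × 62 = 12.4 children. The rest of the calculation does not decide this point.

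**Inputs.** From the article: 31 per arm, 20% dropout, two-sided 0.05 (so 2.5% on the noninferiority side). Assumed, because the article gives no value: margin M of 0.5 SD (also 0.8 SD), control gain g_C = 1 SD, the split of withdrawals between arms, and a correlation of 0.5 between outcome and staying in when poor responders leave. The true tuina gain is set at the margin: g_T = 1 − M.

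**LOCF by formula.** If withdrawal is unrelated to outcome and baseline is carried forward, the expected deficit is (1 − w_C)·g_C − (1 − w_T)·g_T, where w is the proportion withdrawn. With M = 0.5:
- 20% in each arm: 0.8 × 1 − 0.8 × 0.5 = 0.40 SD, a shrinkage of 20%.
- 20% in each arm, half of the child's own change carried: 0.9 × 1 − 0.9 × 0.5 = 0.45 SD, a shrinkage of 10%.
- 10% tuina, 30% control: 0.7 × 1 − 0.9 × 0.5 = 0.25 SD.
- 30% tuina, 10% control: 0.9 × 1 − 0.7 × 0.5 = 0.55 SD, so the deficit widens.

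**Error rates.** The table shows a simulation of 40,000 trials per scenario, with a t-based 95% confidence interval and M = 0.5 SD.

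| Withdrawn, tuina / control | Who leaves | Method | Mean deficit (SD) | False noninferiority |
|---|---|---|---|---|
| none | – | all observed | 0.50 | 2.4–2.5% |
| 20% / 20% | at random | LOCF, baseline | 0.40 | 6.4% |
| 20% / 20% | at random | LOCF, half-way value | 0.45 | 4.0% |
| 20% / 20% | at random or poor responders | listwise | 0.50 | 2.5% |
| 10% / 30% | at random | LOCF, baseline | 0.25 | 18.2% |
| 10% / 30% | poor responders | LOCF, baseline | 0.34 | 10.1% |
| 10% / 30% | poor responders | listwise | 0.65 | 0.65% |
| 30% / 10% | at random | LOCF, baseline | 0.55 | 1.5% |
| 30% / 10% | poor responders | LOCF, baseline | 0.46 | 3.5% |
| 30% / 10% | poor responders | listwise | 0.35 | 7.7% |

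Listwise deletion with random withdrawal stays at about 2.5% for every split. In the scenario of 10% / 30% with poor responders leaving, two methods that the article allows give 10.1% and 0.65%.

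With M = 0.8 SD, balanced LOCF from baseline gives a deficit of 0.64 SD and an error of about 10%; with a half-way value it gives 0.72 SD and about 5%. Random LOCF with 30% / 10% then gives 0.9 × 1 − 0.7 × 0.2 = 0.76 SD, so it shrinks the deficit slightly where it widened it at M = 0.5. EM was not simulated.

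**The case against.** A reader might infer that the plan always pulls the arms together and so always favours noninferiority. The figures do not support that. Listwise deletion is unbiased under random withdrawal, and also when poor responders leave both arms equally. With uneven withdrawal it can help or hurt tuina. LOCF can widen the deficit when more children leave the tuina arm. EM has no built-in pull towards equality if data are missing at random. The two primary outcomes can even move in opposite directions: if vision improves while eyes lengthen, carrying baseline forward penalises the arm with more withdrawals on acuity and flatters it on axial length.

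A reader might also infer that withdrawn children are excluded from the analysis. The article does not say so. It says that they leave the trial, and the case report form records concomitant medication and dropout. Loss of their later data is the natural reading, since nothing provides for further measurement, but it is an inference.

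The size is uncertain too. The 20% covers dropout from every cause, and no rate is given for uptake of other interventions. A week 4 visit exists, so the value carried would often be later than baseline and the effect smaller. The Abstract says that statisticians are blinded, which limits a choice of method made to suit the result. Detail on analysis sets may properly sit in an analysis plan.

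All of this bears on direction and size. It leaves two stated provisions: a withdrawal rule with no continued measurement, and three methods with no rule for choosing.

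**Conclusion.** The concern holds as a risk of bias in either direction. One direction is predictable: LOCF with balanced withdrawals favours noninferiority. With 20% per arm carrying baseline forward, a control gain of 1 SD and a margin of 0.5 SD, the deficit shrinks by 20% and false noninferiority rises from 2.5% to about 6%, or to about 4% with a half-way value. These figures illustrate what could happen and are not forecasts, because margin, gain and withdrawal pattern are all assumed. The firmer result is that permitted methods applied to the same withdrawals can give very different error rates, so the method has to be fixed in advance and the outcomes have to be collected.

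**What to change.** **Selection of Therapists and Participants.** Replace withdrawal from the trial with this: use of another intervention is recorded and serves only to define a supporting per-protocol set. Outcomes are still measured at the scheduled week 4, 8 and 10 visits wherever the family still consents, which respects the right to withdraw stated under Recruitment Strategy and Ethical Considerations. This change concerns measurement only; it does not alter which treatment a child may receive.

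**Data Analysis.** Analyse all randomised children by assigned arm with one prespecified primary method, either a mixed model for repeated measures with baseline or multiple imputation. Remove LOCF, single EM and listwise deletion as primary options. Add one sensitivity analysis for data not missing at random.

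**Cost.** Follow-up effort at visits already scheduled, and a little more analysis work. Recruitment is planned to run to October 2026, so the change can still protect the outcomes of children yet to be enrolled.
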